## Method/design

2

This study is a prospective randomized controlled clinical trial. The purpose of the proposed study is to investigate the efficacy of traditional Chinese medicine compresses combined with intermittent traction on CSR. The Principal Investigator (PI) is responsible for the entire project and organizes the steering committee meeting. The independent steering committee will be responsible for the safety of participants, meetings, recruitment and follow-up of participants, and quality control. The coordination center is responsible for communicating agreement changes and providing materials. The trial includes a 4-week treatment period and a 4-week follow-up period. After randomization, the patients will receive 2 courses of treatment within 4 weeks. Efficacy evaluations will be performed 7 days after the start of treatment, 14 days after treatment, 21 days after treatment, and 28 days after treatment (Fig. 1; Additional File 1).

**Figure 1 F1:**
[figure not shown]
Consort flow diagram.

### Eligibility criteria

2.1

#### Inclusion criteria

2.1.1

1.Meet the criteria for CSR;2.Informed consent and signed informed consent form;3.Be between 18 to 70 years old;4.Patients who voluntarily accept the treatment plan of this study.

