#### Exclusion criteria

2.1.2

1.Patients who do not meet the diagnostic criteria, and patients who are under 18 years old or over 70 years old;2.Those who are allergic to traditional Chinese medicine;3.Women during pregnancy and lactation;4.Patients who have undergone cervical spine surgery or have a history of neck trauma;5.Patients with serious primary diseases or mental illnesses such as heart, brain, liver, kidney and hematopoietic system;6.Patients with skin diseases and infectious diseases;7.A history of diabetes and poor blood sugar control;8.Patients whose condition is serious and are not suitable for conservative treatment or who require surgical treatment;9.Patients who have received other treatments, which may affect the observation of treatment effect indicators in this study.

Participants in the patient recruitment program will be recruited from Longhua Hospital affiliated to Shanghai University of Traditional Chinese Medicine. The expected participants will be interviewed by the coordinator and notified of their eligibility criteria and procedures. Those who are eligible and willing to participate in the study will first be screened through a baseline assessment, and then diagnosed based on clinical manifestations, physical examination, and imaging. Participants will be told that participation in the trial is absolutely voluntary and can withdraw from the trial at any time. If you exit, the collected data will not be deleted and will be used for final analysis. A data compilation table containing all variables of interest and all potential risks will be completed by the corresponding research center. The information obtained will be stored in an electronic database for subsequent statistical analysis. Recruitment will start in September 2020 and is expected to end in December 2020. The final follow-up work for all participants will be completed on January 31, 2021. See Figure 1 for the participant processing and evaluation timeline.

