#### Outcome measurement

2.1.6

Pain is one of the most common reasons for patients with CSR to see a doctor. Therefore, the Visual Analog Pain Scale (VAS) will be chosen as the main outcome measure for the assessment of the neck and upper limbs. The VAS score is a reliable and effective method of pain measurement. There is a 100 mm long horizontal line. The left side records “no pain” (score 0), and the right side records “pain is severe and intolerable” (score 10). The patient is required to place a mark corresponding to its current pain level on the horizontal line (the most severe pain at rest and during exercise),^[11]^ and then determine the VAS score by measurement.

Neck Disability Index (NDI)^[12]^ is one of the most commonly used indexes to evaluate patients neck dysfunction. The NDI score includes 4 subjective symptoms (neck pain intensity, headache, concentration, sleep) and 6 items related to activities of daily living (weightlifting, work, driving or cycling, entertainment, personal care, reading). Each item has 6 levels of responses, each with a score of 0 to 5, 0 means no disability, 5 means severe disability. The lowest total NDI score is 0 points, and the highest is 50 points; the higher the score, the more serious the degree of dysfunction. This study adopted all dimensions of NDI score.

Tanaka Yasuhisa Cervical Spondylopathy Symptom Scale is the “Nerve Root Cervical Spondylopathy Symptom Scale” proposed by the Japanese scholar Hisasu Tanaka. It compares the improvement index before and after treatment for evaluation: improvement rate = (points after treatment-points before treatment)/(20 -Points before treatment)∗100%.

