## Discussion

3

The clinical features of CSR are that the pain range is consistent with the compressed spinal nerve area, mainly pain, numbness, and hypoesthesia. In severe cases, radicular weakness, and muscle atrophy may occur. After the occurrence of CSR, a large number of inflammatory factors are released from the damaged tissue, which stimulates the nerve root and causes radicular pain symptoms.^[13]^ At the same time, it activates a variety of cell signal transduction pathways, cytokines and receptor proteins in the body, which in turn can induce interleukin-1β (IL-1β), interleukin-6 (IL-6), and tumor necrosis factor- α (TNF-α) and other pro-inflammatory cytokines are secreted to mediate inflammation and form a vicious circle of inflammation.^[13]^ The heat generated by herb compresses causes blood vessels to dilate and muscles relax. Heat therapy is a common alternative therapy to improve blood circulation and local muscle spasms. The various ingredients of herb have a variety of analgesic and anti-inflammatory properties. The herb in this research contain Corydalis, Yang Bin, etc.^[14]^ When studying the extracts of Chinese medicine Corydalis Corydalis, they found that Corydalis extracts can exert the same effect as NLRP3 inhibitors. Inhibit NLRP3 inflammasome signaling pathway protein expression. The NLRP3 inflammasome signaling pathway can be widely involved in the body's inflammatory response and promote the synthesis and secretion of inflammatory factors such as prostaglandin E2 (PGE2), phospholipase A2 (PLA2), IL-6, and TNF-α.^[15]^ Corydalis extract inhibits NALP3 and then inhibits the inflammatory response, relieves the inflammatory response caused by nerve root compression, and reduces secondary spinal cord injury.

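### No minimum baseline pain is set for entry although pain VAS is the main outcome, so patients near the floor of the scale can be randomised and sensitivity to the herbal effect is reduced

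*Protocol article*

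**What the plan says.** Section 2.1.1 lists four inclusion criteria: "1.Meet the criteria for CSR;2.Informed consent and signed informed consent form;3.Be between 18 to 70 years old", and finally acceptance of the treatment plan. None refers to a pain level.

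Section 2.1.2 lists nine exclusions. The only one that concerns severity is an upper limit: "8.Patients whose condition is serious and are not suitable for conservative treatment or who require surgical treatment". The same section says that candidates are "then diagnosed based on clinical manifestations, physical examination, and imaging". The diagnostic criteria for CSR are not reproduced.

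Section 2.1.6 states that "the Visual Analog Pain Scale (VAS) will be chosen as the main outcome measure for the assessment of the neck and upper limbs". The line runs from 0 to 10, and its lower end is fixed at no pain: "The left side records “no pain” (score 0". The reason given for choosing pain is that "Pain is one of the most common reasons for patients with CSR to see a doctor". The Discussion describes the clinical features of CSR as "mainly pain, numbness, and hypoesthesia".

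Section 2.1.5 fixes 50 patients per arm. Section 2.2.1 names a two-sided Student t test at 0.05, or a nonparametric test if the data are not normal. It does not mention adjustment for baseline, and it does not say whether final scores or changes are compared.

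**The concern.** Both arms receive traction and heat (section 2.1.4), so the trial has to detect the increment due to the herbs alone, measured mainly on pain VAS. A patient who enters at VAS 1 can fall by at most 1 point in either arm. The article itself names features of CSR other than pain, and nothing printed keeps out a patient who has mainly those.

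Two things follow if some such patients are enrolled. The average difference between arms shrinks, because part of the sample has little room to improve. Scores also become more spread out, because the sample now runs from almost no pain to severe pain. An analysis that ignores baseline puts that spread into its error term. With only 50 per arm, a null result could then partly reflect who was enrolled and how the scores were compared, and not only the compress.

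**Working it through.** **The plan's own figure.** The 50 per arm cannot be reproduced, because the article shows no target difference, SD, power or dropout. Working backwards, the difference detectable with 80% power at two-sided 0.05 is (1.960 + 0.842) × √(2/50) = 2.802 × 0.20 = 0.56 SD.

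**Illustration: inputs.** From the document: 50 per arm, two-sided 0.05, VAS 0 to 10, t test. All of the following are assumptions:
- Patients with pain have baseline VAS from a normal distribution with mean 6 and SD 1.5, truncated to 3–10.
- Low-pain patients have baseline VAS uniform on 0–3 and make up a share f of the sample.
- Scores fall by 40% in both arms, and the herbs take off 1 further point.
- Residual SD is 1.5, and final scores cannot go below 0.

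**Formula.** d = mean difference ÷ SD of the score analysed; power ≈ Φ(d × √25 − 1.98). Means and SDs come from 2,000,000 simulated patients per arm.

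| f | Mean difference | SD of final score | d | Power, t test on final scores | Power, t test on changes | Power, baseline-adjusted |
|---|---|---|---|---|---|---|
| 0% | 0.96 | 1.66 | 0.58 | 82% | 86% | 91% |
| 10% | 0.93 | 1.75 | 0.53 | 75% | 78% | 90% |
| 20% | 0.89 | 1.81 | 0.49 | 69% | 71% | 89% |
| 30% | 0.86 | 1.84 | 0.47 | 64% | 66% | 88–89% |

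**Reading the 20% row.**
1. Low-pain patients still show an arm difference of about 0.60 points, against 0.96 in patients with pain. The mean difference therefore shrinks by 0.20 × (1 − 0.60/0.96) = 7.5%.
2. The SD of final scores rises from 1.66 to 1.81, or 9%.
3. With the SD held at 1.66, d = 0.892/1.66 = 0.537 and power = Φ(2.69 − 1.98) = 76%. The smaller mean difference thus accounts for 82% → 76%, and the wider spread for 76% → 69%.
4. With baseline adjustment the residual SD is 1.45 at f = 0% and 1.38 at f = 20%. Hence d goes from 0.963/1.451 = 0.664 to 0.892/1.382 = 0.645, and power from 91% to 89%.

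**A harsher assumption.** Suppose that low-pain patients show no effect at all and the SD stays the same. The detectable 0.56 SD becomes 0.56 × (1 − f), and power = Φ(0.56 × (1 − f)/0.20 − 1.96). Power then falls from 80% to 71%, 61% and 50% at f = 10%, 20% and 30%. In this version the loss lies in the mean difference, so only an entry minimum would prevent it.

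**The case against.** The case on the other side has real weight, in five parts.

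- **The diagnostic criteria are not shown.** They may require radicular pain. No share of low-pain patients is given, and 0% fits the text as well as 20%. This stands: such patients can be randomised, but the document does not show that they are.
- **A reader might infer that low-pain patients cannot show the benefit and add nothing.** The illustration does not support that. They still contribute about 0.6 points of arm difference under its assumptions. The zero-effect version is a separate and harsher assumption.
- **A reader might infer a loss equal to more than a quarter of the sample at f = 20%**, since (0.493/0.580)² = 0.72. That figure belongs to an unadjusted comparison of final scores. With baseline adjustment the ratio is (0.645/0.664)² = 0.94, a loss of about 6%.
- **A reader might infer that the exclusions cut off the patients with most pain.** The severity exclusion speaks of a serious condition or a need for surgery and does not mention pain. Weakness or another deficit could equally trigger it.
- **Broad entry is legitimate.** The stated purpose in section 2 is efficacy in CSR, and the Neck Disability Index and the 20-point symptom scale are also collected, so a patient with numbness is informative for the trial as a whole. The Discussion places pain first among the features. The VAS asks for the worst pain at rest and in movement, which makes scores near zero less likely. All of this limits the size of the problem. It does not remove the mismatch between open entry and a pain score as main outcome, and the article does not give breadth as its reason.

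**Conclusion.** The point holds as a loss of sensitivity of unknown size. The printed criteria leave entry open at the floor of the main outcome, and the stated test makes no use of baseline. Both push towards finding no difference; neither favours an arm, and nothing here is a contradiction in the document.

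Under the assumed values with 20% low-pain patients, the mean difference falls from 0.96 to 0.89 points and t-test power from about 82% to 69%. Comparing changes instead of final scores gives a similar fall, from 86% to 71%. Added spread is slightly the larger part of the loss, and baseline adjustment brings power to about 89%. In this illustration adjustment alone (89%) therefore does more than an entry minimum alone (82%), and both together give 91%. The ranking depends on low-pain patients keeping part of the effect; if they show none, the entry minimum matters more. All these figures rest on assumed VAS distributions and an assumed 1-point effect, because the article supplies neither.

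**What to change.** 1. **Eligibility (2.1.1).** Add a criterion requiring a minimum baseline VAS, measured before randomisation. The investigators should choose the cut-off and justify it.
2. **Analysis (2.2.1).** Compare VAS between arms adjusted for baseline VAS, for example by ANCOVA, in place of the plain t test.
3. **If recruitment is already complete.** Section 2.1.2 puts the end of recruitment in December 2020, and the article is dated 29 January 2021, so this may be the case that applies. Keep every randomised patient in the baseline-adjusted main analysis, and state in advance a supporting analysis of patients at or above the minimum. Because the subgroup is defined by a score taken before randomisation, the comparison between arms remains a randomised one. The trial is not blinded, so the cut-off should be fixed before outcomes are looked at by arm.

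**Cost.** The VAS is already taken at baseline, so there is no new measurement. Some candidates are turned away: if 20% fell below the minimum, 100/0.80 = 125 otherwise eligible candidates would be needed to randomise 100. The conclusion would then apply to CSR patients with pain, not to all CSR. The adjusted analysis costs nothing beyond a changed line of text.

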#### Exclusion criteria

2.1.2

1.Patients who do not meet the diagnostic criteria, and patients who are under 18 years old or over 70 years old;2.Those who are allergic to traditional Chinese medicine;3.Women during pregnancy and lactation;4.Patients who have undergone cervical spine surgery or have a history of neck trauma;5.Patients with serious primary diseases or mental illnesses such as heart, brain, liver, kidney and hematopoietic system;6.Patients with skin diseases and infectious diseases;7.A history of diabetes and poor blood sugar control;8.Patients whose condition is serious and are not suitable for conservative treatment or who require surgical treatment;9.Patients who have received other treatments, which may affect the observation of treatment effect indicators in this study.

Participants in the patient recruitment program will be recruited from Longhua Hospital affiliated to Shanghai University of Traditional Chinese Medicine. The expected participants will be interviewed by the coordinator and notified of their eligibility criteria and procedures. Those who are eligible and willing to participate in the study will first be screened through a baseline assessment, and then diagnosed based on clinical manifestations, physical examination, and imaging. Participants will be told that participation in the trial is absolutely voluntary and can withdraw from the trial at any time. If you exit, the collected data will not be deleted and will be used for final analysis. A data compilation table containing all variables of interest and all potential risks will be completed by the corresponding research center. The information obtained will be stored in an electronic database for subsequent statistical analysis. Recruitment will start in September 2020 and is expected to end in December 2020. The final follow-up work for all participants will be completed on January 31, 2021. See Figure 1 for the participant processing and evaluation timeline.

#### Ethics approval and consent to participate

2.1.3

This study will be conducted in accordance with the principles of the Helsinki Clinical Research Declaration.^[8]^ The trial protocol has been approved by the Research Ethics Committee of Longhua Hospital affiliated to Shanghai University of Traditional Chinese Medicine (2020LCSY059). All participants will have enough time to make a decision to sign the consent form before the study.^[9,10]^ This agreement has been registered on Clinical Trials (ClinicalTrials.gov, ID: ChiCTR2000037976).

#### Intervention

2.1.4

The control group will be treated with intermittent cervical traction combined with hot compresses (device name: intelligent warm traction system, model YK-60000D), and the traction angle will be 10° to 15°; its starting mass will be 3 to 6 kg, according to the condition and the patient's The degree of tolerance can gradually increase, up to 8 to 12 kg; the traction time is 90 seconds, and the intermittent time is 10 seconds; the traction is used for hot compress treatment with an instrument matching hot compress bag, the temperature is controlled at 40 to 50°C, and the neck is applied externally. Once every day, 20 minutes times, a week of treatment for 5 days, 14 days as a course of treatment, a total of 2 courses of treatment; curative effect evaluation on 7 days, 14 days, 21 days, and 28 days after the start of treatment.

The intervention group will be treated with intermittent cervical traction combines with traditional Chinese medicine hot compress, and the traction method is the same as the control group. Hot compress herbs include: Corydalis, Tougucao, Frankincense, Myrrh, Angelica, Sichuan pepper, Safflower, Ligusticum chuanxiong, Licorice, Weilingxian, Parsnip, Angelica dahurica, first soak in appropriate amount of warm water and steam it in a steamer for 10 minutes. The temperature of hot pack is controlled at 40 to 50°C, and applies traditional Chinese medicine to the neck. Once a day, 20 minutes times, a week of treatment for 5 days, 14 days as the efficacy evaluation, 7 days, 14 days, 21 days, and 28 days after the start of treatment (Fig. 2; Additional File 2).

**Figure 2 F2:**
[figure not shown]
Baseline and follow-up assessments.

#### Randomization and allocation

2.1.5

After screening, patients will be randomly divided into 2 groups with a 1:1 allocation ratio. Randomization will be based on the Statistical Social Science Software Package (SPSS) software (version 21.0), generating random numbers, and patients will be randomly divided into treatment group (50 cases) and control group (50 cases).

#### Outcome measurement

2.1.6

Pain is one of the most common reasons for patients with CSR to see a doctor. Therefore, the Visual Analog Pain Scale (VAS) will be chosen as the main outcome measure for the assessment of the neck and upper limbs. The VAS score is a reliable and effective method of pain measurement. There is a 100 mm long horizontal line. The left side records “no pain” (score 0), and the right side records “pain is severe and intolerable” (score 10). The patient is required to place a mark corresponding to its current pain level on the horizontal line (the most severe pain at rest and during exercise),^[11]^ and then determine the VAS score by measurement.

Neck Disability Index (NDI)^[12]^ is one of the most commonly used indexes to evaluate patients neck dysfunction. The NDI score includes 4 subjective symptoms (neck pain intensity, headache, concentration, sleep) and 6 items related to activities of daily living (weightlifting, work, driving or cycling, entertainment, personal care, reading). Each item has 6 levels of responses, each with a score of 0 to 5, 0 means no disability, 5 means severe disability. The lowest total NDI score is 0 points, and the highest is 50 points; the higher the score, the more serious the degree of dysfunction. This study adopted all dimensions of NDI score.

Tanaka Yasuhisa Cervical Spondylopathy Symptom Scale is the “Nerve Root Cervical Spondylopathy Symptom Scale” proposed by the Japanese scholar Hisasu Tanaka. It compares the improvement index before and after treatment for evaluation: improvement rate = (points after treatment-points before treatment)/(20 -Points before treatment)∗100%.

#### Assess safety

2.1.7

To ensure the safety of participants, the data collection process will be supervised by the project leader. At each supervision, participants will be required to stay in the hospital for 30 minutes after treatment and asked about any signs of acute adverse reactions during the study. Side effects will be recorded at every visit during treatment.

### Sample size calculation

2.2

#### Statistical analysis

2.2.1

Trained statisticians will use intentional processing methods for effectiveness and safety analysis. In addition, the final outcome observation index method will be applied to deal with missing values. All statistical analysis will be performed by the SPSS 21.0. The statistical test is two-way, *P* < .05 is statistically significant. The mean ± standard deviation will be used to describe continuous variables. This percentage is used to describe the variable. Continuous variables that follow a normal distribution will be analyzed by Student *t* test; otherwise, nonparametric tests will be used to compare group differences.

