## Abstract

Cervical spondylotic radiculopathy (CSR) is the most common type of cervical spondylosis, accounting for about 60% of the incidence of cervical spondylosis. Both cervical traction and traditional Chinese medicine hot compress are common and effective treatment for CSR. This study will be performed to investigate the effect of a combination of cervical traction and traditional Chinese medicine hot compress on CSR. In this non-blinded, randomized controlled trial, 100 eligible patients will be randomly divided into a treatment group (intermittent cervical traction combines with traditional Chinese medicine hot compress) and a control group (intermittent cervical traction combined with hot compresses). Before and after the intervention, the Visual Analog Scale score, Neck Disability Index score, and 20-score scale of symptoms will be evaluated at baseline and at 7, 14, 21, and 28 days. During the treatment period, any signs of acute adverse events, such as paralysis of aggravated pain, nausea, dizzy, and even syncope, will be recorded at each visit. Although intermittent cervical traction and traditional Chinese medicine hot compress have been used in the treatment of CSR in China for many years, there is no consensus on its effectiveness of combination therapy. This experiment will provide convincing evidence of the efficacy of intermittent cervical traction combined with traditional Chinese medicine hot compress in the treatment of CSR.

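### The one missing-data rule, most naturally read as last observation carried forward, can bias the VAS comparison in either direction; name it plainly and analyse all weekly scores instead

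*Protocol article*

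**What the plan says.** Section 2.2.1 (Statistical analysis) states: "Trained statisticians will use intentional processing methods for effectiveness and safety analysis". This reads as a translation of intention to treat. The next sentence gives the only rule for missing data: "the final outcome observation index method will be applied to deal with missing values". Groups are then compared by Student's t test, or by a nonparametric test if the data are not normal, two-sided at 5%. No model for the repeated visits is mentioned.

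Four other statements bear on how that rule would work:

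- Section 2.1.6: "the Visual Analog Pain Scale (VAS) will be chosen as the main outcome measure". The patient marks the scale.
- Abstract: the scores "will be evaluated at baseline and at 7, 14, 21, and 28 days". No visit is named as primary; day 28 is the last one listed.
- Abstract: "In this non-blinded, randomized controlled trial".
- Section 2.1.2, in the recruitment paragraph, on participants who leave: "the collected data will not be deleted and will be used for final analysis".

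Section 2.2.3 says dropouts and their reasons will be recorded. No dropout rate is given, overall or by arm.

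**The concern.** Under LOCF a patient who leaves after day 7 keeps the day-7 pain score at every later visit. The Abstract describes both traction and the herbal compress as established treatments that work, and both arms receive traction plus heat. Falling pain in both arms is therefore the trial's own premise. On that premise a carried-forward score overstates later pain, and the arm that loses more patients looks worse for that reason alone.

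An open trial with about 20 treatment sessions (5 days a week for 4 weeks) has a realistic risk of uneven loss. At stake are the 5% error rate of the main comparison and the size of the estimated effect. LOCF could produce an apparent benefit or hide a real one.

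**Working it through.** **Inputs from the article.** 50 per arm; two-sided 5%; t test; assessments at days 0, 7, 14, 21 and 28. The article states no figure on missing data, so there is none to reproduce.

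**Assumed inputs.** Mean VAS 6, 5, 4.2, 3.5 and 3 at the five assessments; SD 1.8; dropout random within arm. Day 28 is used for illustration.

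**Bias with no true effect.** Difference (herbal minus control) = (herbal dropout − control dropout) × (mean of the carried score − day-28 mean). The second factor depends on when patients leave:

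- Last score at day 7: 5 − 3 = 2.0
- Last score equally at days 7, 14, 21: (5 + 4.2 + 3.5)/3 − 3 = 1.23
- Last score equally at days 0, 7, 14, 21: (6 + 5 + 4.2 + 3.5)/4 − 3 = 1.675

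Simulated t tests on LOCF-filled day-28 scores (5,000 or 8,000 trials per row):

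| Dropout, herbal v control | Last score | Formula | Simulated bias | Type I error |
|---|---|---|---|---|
| 5% v 15% | days 7–21 | −0.10 × 1.23 = −0.12 | −0.13 | 6.5% |
| 5% v 15% | days 0–21 | −0.10 × 1.675 = −0.17 | −0.18 | 7.0% |
| 5% v 20% | days 0–21 | −0.15 × 1.675 = −0.25 | −0.25 | 9.6% |
| 5% v 15% | day 7 | −0.10 × 2.0 = −0.20 | −0.19 | 8.3% |
| 5% v 20% | day 7 | −0.15 × 2.0 = −0.30 | −0.30 | 12.8% |
| 20% v 20% | days 0–21 | 0 | 0.00 | 4.9% |

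Swapping the arms reverses the sign.

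**Hand check of one error rate (5% v 20%, day 7).** Mixing day-7 and day-28 scores adds d(1 − d) × 2² to the variance. Control: 3.24 + 0.16 × 4 = 3.88. Herbal: 3.24 + 0.0475 × 4 = 3.43. SE = √((3.88 + 3.43)/50) = 0.38. Shift = 0.30/0.38 = 0.78 SE. Rejection ≈ P(Z > 1.96 − 0.78) + P(Z < −1.96 − 0.78) ≈ 0.12, close to the simulated 12.8%.

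**With a true effect of −1.0 at day 28 that grows in equal steps.** Herbal means are 6, 4.75, 3.7, 2.75 and 2.0. The carried score exceeds the day-28 mean by (6 + 4.75 + 3.7 + 2.75)/4 − 2 = 2.30 in the herbal arm and by 1.675 in the control arm.

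- 20% v 5% (herbal v control): (2 + 0.20 × 2.30) − (3 + 0.05 × 1.675) = 2.46 − 3.084 = −0.62. Simulated power falls from about 79% without dropout to 35%.
- 20% v 20%: 2.46 − (3 + 0.20 × 1.675) = 2.46 − 3.335 = −0.875, about −0.87. Simulated power is about 56%.
- 5% v 20%: (2 + 0.05 × 2.30) − 3.335 = 2.115 − 3.335 = −1.22.

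**Comparator.** A likelihood estimate of the day-28 difference from all observed visits was run over 3,000 trials with no true effect. Correlation between adjacent visits was taken as 0.77, and last scores fell equally at days 0 to 21. The mean difference was −0.004 at 5% v 20% and −0.001 at 10% v 30%; LOCF gives −0.25 and −0.34. The SD of the likelihood estimate at 5% v 20% was 0.385. A true −1.0 with the same pair of rates, in either order, therefore has power of roughly P(Z > 1.96 − 1/0.385) = P(Z > −0.64) ≈ 74%. Most of the fall to 35% comes from LOCF and not from the lost data.

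**The case against.** The article never says LOCF. The phrase is probably a poor translation, and the sponsor may mean something else. This stands, and it is why naming the method comes first in the fix.

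The harm depends on figures that the article does not give. Rates of 15% to 20% against 5% are assumed, as are the VAS course and SD. With equal dropout and no true effect there is no bias. This stands too, and it limits the severity.

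A reader might infer that control patients will leave sooner, so that LOCF will favour the herbal compress. The documents do not support this. Under section 2.1.4 the control arm receives the same traction and a heated pack in the same 40 to 50°C range, so it is an active package. Nothing in the text says which arm will lose more.

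A reader might also say that treating filled-in scores as observed understates the uncertainty and so inflates the error rate. The calculation does not show that: with equal dropout the error rate stays near 5%. The inflation in the unequal scenarios comes from the shift in means.

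Finally, a separate analysis plan may exist, and sensitivity analyses are often left to it. Their absence here is not the point. The point is the rule that the article itself fixes. Keeping data from patients who leave is sound, and a mixed model needs those data as well.

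**Conclusion.** The point holds as a should-fix. The article fixes one poorly worded missing-data rule, most naturally LOCF, for an outcome expected to improve week by week in an open trial.

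Under the assumed course and SD, 5% v 15% to 20% dropout shifts the day-28 difference by about 0.13 to 0.25 points with a type I error of about 6.5% to 10% when dropout is spread over visits. If everyone leaves after day 7, the figures are about 0.2 to 0.3 points and 8% to 13%. For scale, 50 per arm detects about 0.56 SD at 80% power, or 0.56 × 1.8 = 1.0 point. The bias would favour the arm with less dropout, given similar timing in both. A growing effect of −1.0 is also distorted: to about −0.62 with 20% v 5% dropout (herbal v control), and to about −0.87 with equal 20% dropout.

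It would be too much to infer that the stated 5% level will be exceeded or that the day-28 result will be biased in a known direction. The article gives no dropout rate and does not name day 28 as primary. The same mechanism applies at days 14 and 21.

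**What to change.** 1. State the missing-data method in plain terms.
2. Replace LOCF as the main method with a likelihood-based mixed model for repeated measures on all observed weekly VAS scores, with baseline, arm, visit and arm-by-visit terms. Name the visit contrast that serves as the primary result, for example day 28, the last assessment listed. Keep LOCF at most as a sensitivity analysis.
3. Add one delta-adjusted sensitivity analysis, because the model removes the bias only if data are missing at random. It does not cover dropout driven by pain that was never recorded.

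The weekly scores are already planned, and the MIXED procedure in SPSS, the package named in section 2.2.1, fits the model. The cost is a few hours of extra analysis and reliance on the missing-at-random assumption.
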